### Outcome Measures

All interviews and questionnaires seek to understand the lived experience of IPV within the context of pregnancy and childbirth, as well as the impact of CBT on the five primary study objectives described previously. Specifically, it is expected that this study will ascertain the impact of CBT on a) maternal mental health*,* and b) maternal-infant attachment. These outcomes will be measured using the PTSD Checklist (PCL-5), EPDS, Spielberger State-Trait Anxiety Inventory (STAI), World Health Organization Quality of Life Brief Assessment (WHOQOL-BREF), Maternal Attachment Inventory (MAI) and Proactive Coping Inventory (PCI). Each will be discussed in turn.

#### PTSD Checklist (PCL-5)

The PCL-5 is a PTSD Checklist for DSM-V symptomatology consisting of 20 items in a standardized self-report measure that assesses the presence and severity of PTSD [33]. Respondents indicate how much they have been bothered by a particular symptom over the past month using a 5-point Likert scale, with responses varying between 0 (not at all) and 4 (extremely). A total symptom severity score—ranging from 0 to 80—is obtained by summing the self-reported ratings for all 20 items, with higher scores indicating greater PTSD symptomatology. Based upon thorough psychometric evaluation [33], the PCL-5 has demonstrated excellent internal consistency (alpha=.94) and construct validity.

#### Edinburgh Postnatal Depression Scale

Postpartum depression will be measured using the EPDS—a 10-item screening questionnaire used to identify symptoms of a depressive disorder, as outlined in the DSM-5 [34]. Women are asked to answer each question by selecting the response that best describes their feelings during the previous 7 days. Responses are assigned points from 0 to 4, with higher values corresponding to more severe depressive symptomatology. Points from each question are summed, with total scores ranging from 0 to 30. The EPDS has been used consistently among perinatal practitioners since its inception, and is widely recognized as a valid and reliable screening tool with strong internal consistency (alpha=.83-.87) [35]. The EPDS has a cut score of 15 or more for antenatal women indicating a major depressive episode.

#### Spielberger State-Trait Anxiety Inventory

Anxiety among at-risk women will be assessed using the STAI [36]. The STAI is an introspective psychological instrument consisting of 40 self-reported items, separated into two subscales (ie, A-State and A-Trait), each with 20 items. “State anxiety” is defined as a transient momentary emotional status that results from situational stress, while “trait anxiety” represents a predisposition to react with anxiety in stressful situations [37]. All items are scored using a 4-point Likert scale (1-4), with totals ranging from 20 to 80 for each subscale, with higher scores suggestive of greater anxiety. Considerable evidence [36] attests to the construct and concurrent validity of the STAI (alpha=.86-.91).

#### World Health Organization Quality of Life Brief Assessment

Maternal quality of life (QOL) will be assessed using the WHOQOL-BREF, an instrument comprised of 26 items measuring the following four domains: physical health, psychological health, social relationships, and environment. Responses for each question range from 1 to 5 along a Likert-type scale, with higher scores corresponding to a greater self-perceived QOL. The WHOQOL-BREF has been found to have strong discriminant validity (*r*>.45) and internal consistency (alpha=.84) [38].

#### Maternal Attachment Inventory

Maternal-infant attachment will be evaluated using the MAI [39]. The MAI is a 26-item self-report instrument is measured on a four-point Likert scale, ranging from a) almost always, b) often, c) sometimes, and d) almost never. A total score is obtained by converting subjects’ responses to corresponding numeric values as follows: a) 4 points, b) 3 points, c) 2 points, and d) 1 point. All items are summed, resulting in scores ranging from 26 to 104. Higher scores indicate stronger feelings of attachment toward the newborn child. This instrument was initially tested in a sample of 196 women at one month postpartum, resulting in acceptable internal consistency and validity (alpha=.85) [39].

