**Methods:**

The Promoting Attachment Through Healing (PATH) study will use a mixed-methods approach grounded in an intersectional feminist framework to explore the effectiveness of trauma-informed CBT for pregnant survivors of IPV. Study participants will be recruited through the hospital-based Perinatal Mental Health Clinic (London, Ontario, Canada). A feasibility sample of 20 pregnant women (cohort 1) will be selected to engage in an eight-session antenatal CBT intervention facilitated by the program’s perinatal clinical nurse specialist, with evaluation at baseline, at two months postpartum (intervention and online questionnaire), and at six and twelve months postpartum (online questionnaire only). Concurrently, we will conduct a retrospective audit of 100 medical charts (cohort 2; 50 charts of perinatal women who received CBT and 50 charts of women who did not receive perinatal CBT) from the past five years. The efficacy of the intervention will be based on a reduction of mental illness symptomatology, improved maternal-infant attachment, maternal coping, and maternal quality of life. Additionally, the feasibility of the protocol and acceptability of the intervention from the women’s perspective will be examined. Inductive content analysis of all qualitative data will be used to determine common themes. Additionally, descriptive statistics, including measures of central tendency and dispersion, will be computed for all continuous variables. Alternatively, frequency tables will be constructed for all categorical variables.

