### Data Collection

Data collection will occur simultaneously for both cohorts.

#### Cohort 1

Data collection will occur at baseline (T1; prior to the PCNS-delivered CBT and during pregnancy), two (T2), six (T3), and twelve (T4) months postpartum. At T1 and T2, a mixed-method data collection model will be utilized wherein women will complete a semistructured interview for approximately one hour (audio-recorded) and complete a short demographic survey. At T3 and T4, participants will be sent an electronic link to complete a questionnaire (or alternatively, if this is thought to be unsafe, a member of the research team will meet with the participant to complete a hardcopy version).

During the T1 data collection interaction, the study protocol will be thoroughly described and consent to participate will be obtained. Throughout the data collection period (T1-T4), a detailed safety plan will be reviewed (updated as needed), and participants will be provided a $25 honorarium (retail gift card) in recognition of their contribution to the study. To further reduce potential barriers to involvement, those in need of reimbursement for childcare or transportation expenses to attend the in-person interviews will be offered $15 and $10, respectively.

#### Cohort 2

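### The Maternal Attachment Inventory has neither a pre-CBT value nor a standard-care comparator, so objective 4 and the attachment efficacy criterion claim more than it can support

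*Protocol article*

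**What the plan says.** The Objectives section lists, as the fourth of five aims, determining the impact of antenatal CBT on maternal-infant attachment. The abstract (Methods) and Study Rationale and Future Direction both name better attachment among the outcomes by which efficacy will be judged.

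Outcome Measures names six instruments. One concerns attachment: "Maternal-infant attachment will be evaluated using the MAI [39". On meaning, the article says: "Higher scores indicate stronger feelings of attachment toward the newborn child". On testing: "This instrument was initially tested in a sample of 196 women at one month postpartum". On scoring: "All items are summed, resulting in scores ranging from 26 to 104".

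The cohort 1 schedule in Data Collection is: "Data collection will occur at baseline (T1; prior to the PCNS-delivered CBT and during pregnancy), two (T2), six (T3), and twelve (T4) months postpartum". Under Design, the 20 women of cohort 1 are all invited to the eight-session antenatal programme, and there is no concurrent control group.

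Cohort 2 is a retrospective audit of 100 charts, 50 with CBT and 50 with standard care. Data Collection says that it needs no patient contact. Its abstraction list includes an item for evidence of maternal-infant attachment, without a scale. The MAI is not on the list.

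Statistical Analysis plans GEE to assess effectiveness over time and against standard care.

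**The concern.** An impact of CBT on an outcome can be estimated only from a contrast: before against after, or treated against untreated. The MAI asks about a newborn, and cohort 1 has no newborn until CBT is finished. The group meant to supply the untreated side is never given the MAI. If both contrasts are missing, what is left is a series of postpartum readings in treated women.

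At stake is how those readings are interpreted. Attachment is in the study's name, and the Conclusions link supported hypotheses to scale-up and stronger mother-infant bonds. With improved attachment as an efficacy criterion and no rule for reading MAI change, a rise between two and twelve months postpartum could be taken as benefit from CBT, although it carries no information about CBT.

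**Working it through.** **Scale arithmetic.** The article gives 26 items scored 1 to 4. Minimum 26 × 1 = 26; maximum 26 × 4 = 104. This reproduces the stated range. The scoring is sound; the difficulty is which contrasts are available.

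**Contrast over time (cohort 1).** Inputs: 20 women (Design); T1 before CBT and in pregnancy, T2 to T4 at 2, 6 and 12 months postpartum (Data Collection); a scale about the newborn (Maternal Attachment Inventory). A mean model with a before/after effect and visit effects is

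E[MAI] = b0 + b1·(after CBT) + b2·(T3) + b3·(T4).

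For the visits at which the MAI can be meaningfully answered, it gives:

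- T2: b0 + b1
- T3: b0 + b1 + b2
- T4: b0 + b1 + b3

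b0 and b1 appear only as a sum, so b1, the before/after effect, cannot be estimated. The rank of the design matrix confirms this:

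| MAI visits | Rows (20 women) | Columns | Rank |
|---|---|---|---|
| T2, T3, T4 | 60 | 4 | 3 |
| T1, T2, T3, T4 on a common scale | 80 | 4 | 4 |

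The estimable quantities are the T2 level and the changes b2 and b3. More women add rows but not rank. The second line would need an attachment measure on a common scale in pregnancy, and none is listed. Even then, b1 would combine CBT with birth and the passage of time, because there is no control.

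**Contrast with standard care.** The article supplies the following attachment data:

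| Group | n | Attachment data |
|---|---|---|
| Cohort 1, CBT | 20 | MAI, meaningful postpartum only |
| Cohort 2, CBT | 50 | unscaled chart evidence |
| Cohort 2, standard care | 50 | unscaled chart evidence |

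No row other than the first has the MAI, so a GEE for the MAI has no standard-care term to estimate. The one attachment variable present in both a treated and an untreated group is the chart item in cohort 2. That supports a crude comparison of 50 with 50, without randomisation and without a defined scale.

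**The case against.** **A postpartum outcome needs no antenatal baseline.** This is right in general. Postpartum MAI in treated and untreated women would give a contrast, so the missing baseline alone is not decisive. Here the comparator is missing as well, and the two gaps together remove the effect.

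**Objective 4 names attachment, not the MAI.** This also stands. A reader might infer that the study has no treatment contrast on attachment at all. The documents do not support that: the cohort 2 chart item allows a CBT versus standard-care comparison, however weak. The limit applies to the MAI.

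**The article never says that the MAI is given at T1.** True. Its unsuitability there is inferred from its target, its one-month postpartum testing and the antenatal timing of T1. A fuller visit schedule would not supply the missing contrast, since both the target and the timing are stated.

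**This is a pilot.** It aims to explore efficacy and inform a later trial, and MAI levels and spread serve that purpose. This supports descriptive reporting. It does not support an efficacy criterion, because the problem is identification, not power. Limitations mentions small sample, single site and reliance on one therapist, but not this.

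**A wider reading to avoid.** For T1 and T2, Data Collection names an interview, "audio-recorded) and complete a short demographic survey", and mentions a questionnaire only at T3 and T4. A reader might infer that no symptom scale has a baseline. The article points the other way: the abstract speaks of evaluation at baseline, Data Collection describes T1 and T2 as mixed-method, and the EPDS section gives a cut score for antenatal women. What remains is a small mismatch at T2, where the abstract has evaluation "at two months postpartum (intervention and online questionnaire), and at six and twelve months postpartum (online questionnaire only".

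**Conclusion.** The point holds for the MAI. It has neither a pre-CBT value nor a standard-care comparator, so neither of the two planned GEE contrasts yields a CBT effect on it. None of the 20 women in cohort 1 can give a meaningful MAI before CBT, and the abstraction list for the 100 charts does not include it. Only the T2 to T4 trend can be estimated, and it cannot be separated from the normal course of attachment after birth. Objective 4 and the improved-attachment criterion, as far as they rest on the MAI, are wrong as written.

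This rests on two assumptions: that the MAI cannot be meaningfully answered before birth, and that the chart evidence contains no MAI scores. The article does not say what that evidence consists of, but an audit without patient contact and with no MAI on its list makes such scores unlikely.

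No sample size or power figure is affected.

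**What to change.** 1. State that the MAI is given at T2, T3 and T4 only.
2. Report it descriptively, as mean and 95% confidence interval at each visit, as input to planning the randomised trial.
3. Remove MAI improvement as an efficacy criterion in the abstract and in Study Rationale and Future Direction, and align the attachment hypothesis in Results.
4. Reword objective 4 to describe postpartum attachment after antenatal CBT.
5. Limit any between-group statement on attachment to the cohort 2 chart comparison (50 CBT, 50 standard care), labelled exploratory and non-randomised.
6. Reconcile the abstract and Data Collection on what is collected at T2. The abstract pairs the questionnaire with the intervention, whereas Data Collection has an interview and a demographic survey.

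Adding an antenatal attachment questionnaire at T1 as a covariate for the T2 MAI would not help: in a single treated arm, a covariate on a different scale gives neither a change score nor a contrast. A real MAI contrast would need the MAI in a standard-care group after birth, which suits the later randomised trial.

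The cost is wording. No visit, form or participant is added.

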#### Proactive Coping Inventory

Maternal coping will be measured using the PCI [40], a multi-dimensional coping scale that assesses how well individuals utilize resources in the development of positive coping strategies to combat distress. The PCI is comprised of seven subscales, each of which assesses a unique dimension: proactive coping, preventive coping, reflective coping, strategic planning, instrumental support seeking, emotional support seeking, and avoidance coping. All items are assessed on a 4-point Likert scale, ranging from 1 (not at all true) to 4 (completely true). Responses are summed to obtain a total score for each subscale, with higher scores reflective of greater proactive coping skills. All subscales were found to have good validity and high internal consistency (alpha=.71-.85) [40].

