## Results

The work reported here is in the proposal phase. Once the protocol is implemented, we will report the results in a follow-up paper. However, we hypothesis that PCNS-delivered CBT will result in decreased PTSD, anxiety, and/or depression symptomatology, and improved maternal-infant attachment, coping, and QOL. We also hypothesize this study will be feasible in terms of fidelity and deliverability, as well as be highly acceptable to participants.

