## Discussion

### Study Rationale and Future Direction

We hypothesize that PCNS-delivered CBT will be effective in treating PTSD symptomatology, depression and anxiety disorders affecting the sample of pregnant women selected [47], thereby contributing to participants’ improved QOL and maternal-infant attachment, and positive child health outcomes following birth.

The PATH study serves to build upon existing health literature that explores the positive impact of CBT for survivors of IPV and those experiencing mental health challenges [48-50] within periods of transformational change associated with pregnancy, childbirth, and motherhood. This feasibility study will help to address a current lack of literature in the area by filling a gap in intervention research aimed at improving the health and QOL of perinatal women who have experienced IPV and have symptomology consistent with PTSD, depression and/or anxiety.

Furthermore, successful implementation will help to determine the feasibility and acceptability of the study methodology and protocol, to support the future full-scale RCT. Efficacy will be determined in relation to a reduction in PTSD, anxiety, and depressive symptoms, and improvement in maternal-infant attachment, maternal coping, and maternal QOL. Feasibility will be assessed in relation to fidelity and resource allocation (from the provider, participant, and system perspectives) and acceptability will be measured in terms of perceived value from the participants’ perspective.

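### The scoring text reads a higher score on every PCI subscale as better coping, although one of the seven subscales is avoidance coping

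*Protocol article*

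**What the plan says.** The Proactive Coping Inventory paragraph under Outcome Measures makes four statements.

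- Purpose: the scale "assesses how well individuals utilize resources in the development of positive coping strategies to combat distress".
- Structure: "The PCI is comprised of seven subscales, each of which assesses a unique dimension". The seven are listed as "proactive coping, preventive coping, reflective coping, strategic planning, instrumental support seeking, emotional support seeking, and avoidance coping".
- Item scoring: all items use a four-point scale, from 1 for not at all true to 4 for completely true.
- Subscale scoring and direction: "Responses are summed to obtain a total score for each subscale, with higher scores reflective of greater proactive coping skills".

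Neither this paragraph nor any other part of the article exempts a subscale from the direction rule or mentions reverse scoring for the PCI.

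Coping counts towards the efficacy claim. The Abstract (Methods) lists maternal coping among the outcomes on which efficacy will be based. The Results section hypothesises "improved maternal-infant attachment, coping, and QOL". Study Rationale and Future Direction says efficacy will be judged partly on "improvement in maternal-infant attachment, maternal coping, and maternal QOL". The article does not say which PCI subscale or subscales stand for maternal coping.

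**The concern.** The direction clause is attached to the score of each subscale, and avoidance coping is one of those subscales. If its items are summed as described, a high score means that the woman endorses avoidance strongly. The text nevertheless interprets a high score as greater proactive coping skill. The label of the subscale and the interpretation given to its score point in opposite directions.

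At stake is the reading of one component of a named efficacy outcome. Someone who applied the sentence as written could report a rise in avoidance after CBT as better coping, and a fall in avoidance, plausibly one of the benefits hoped for, as worse coping. The pilot is meant to support a full-scale randomised trial, so a wrong direction left in the published description could be carried forward into that trial's outcome definitions.

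**Working it through.** The article gives no PCI figure to reproduce, and no sample size, power or alpha figure bears on the point. The check concerns direction only.

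**Inputs, all from the Proactive Coping Inventory paragraph**

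- Number of subscales: 7, of which avoidance coping is one.
- Item score x: 1 to 4, with larger values meaning that the item is more true of the respondent.
- Subscale score: the plain sum of the item scores.
- Number of items in the avoidance subscale, k: not given. It is left as a symbol, and the result does not depend on it.

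**Step 1. Score as stated.** S = Σx over the k avoidance items. The range is k × 1 = k to k × 4 = 4k. A larger S means stronger endorsement of avoidance.

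**Step 2. Score if the items were reversed.** Each item becomes 5 − x, so 1 becomes 4 and 4 becomes 1. The subscale score becomes Σ(5 − x) = 5k − S. Its range is also k to 4k, but a larger value now means less avoidance.

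**Step 3. Effect of a change.** Suppose the stated score moves from S to S + D. The reversed score moves from 5k − S to 5k − S − D, a change of −D. The two scorings give changes of equal size and opposite sign for any k and any D.

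**Step 4. Illustration.** A woman moves from 2 to 3 on every avoidance item.

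| Scoring | Before | After | Change | Reading if higher is better |
|---|---|---|---|---|
| As stated, Σx | 2k | 3k | +k | Better coping |
| Reversed, Σ(5 − x) | 3k | 2k | −k | Worse coping |

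**Step 5. Compare with the text.** The article states the first scoring and attaches to it the interpretation that would need the second. For the other six subscales the check raises no conflict between name and direction. The mismatch is confined to 1 of 7.

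**Step 6. Is direction a detail that the article leaves elsewhere?** No. The paragraphs on the PCL-5, EPDS, STAI, WHOQOL-BREF and MAI each state what a higher score means, and the MAI paragraph also sets out how each response converts to points. The article chose to fix direction here. For the PCI it fixed a single direction for a set of subscales that do not share one.

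**The case against.** Several arguments on the other side have force.

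**The scoring key may reverse the avoidance items.** Keying belongs to the instrument's own source, which is not at hand, and a condensed article may omit it. If the items are reversed, the direction sentence would be correct. This stands as a reason to say that misreporting *could* happen rather than that it will. It does not rescue the text, which gives the item anchors, a plain sum and a direction, and mentions no reversal.

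**The article never says that more avoidance is worse.** Correct; it is an inference from the subscale's name and from the stated aim of measuring positive coping strategies. The inference is a short one. Even without it, avoidance is listed as a dimension distinct from proactive coping, so a high avoidance score cannot simply be taken as evidence of proactive coping skill.

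**The sentence describes an instrument and is not a decision rule.** The Statistical Analysis section plans generalized estimating equations and descriptive statistics, and nowhere says that a rise on a given PCI subscale counts as success. An analyst would have to read a rise on a scale called avoidance coping as good news, against its name. This too limits the likelihood of harm, but leaves the published statement wrong as written.

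**Coping carries little weight here.** It is not among the five numbered objectives. The PCI does not appear in the chart abstraction list for cohort 2, so it seems to concern only the 20 women of cohort 1, and the Limitations section already concedes that the small sample restricts statistical analysis. All of this stands and bears on how much the point matters. Coping is nonetheless named in the efficacy definition.

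**Two stronger readings that the documents do not support.** A reader might infer that the unreversed subscale dilutes an overall coping effect by a calculable fraction. The article plans no PCI total, mean or standardised composite; scores are kept per subscale, so any such fraction would describe an analysis that nobody has proposed. A reader might also infer that the proactive coping subscale should become the only efficacy measure of coping. The defect does not require that, and choosing among subscales is a separate decision for the investigators.

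**Conclusion.** The point holds as an error in a stated rule. The article applies one direction to all seven PCI subscales, and for avoidance coping that direction conflicts with the scoring the same paragraph describes. Read literally, a rise in avoidance could be reported as better coping and a fall as worse coping.

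The size is a reversed sign on 1 of 7 separately scored subscales. A change of D on avoidance would be read as +D when a reading in which higher is better calls for −D. Coping as a whole would not be reversed, and the remaining subscales are unaffected.

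The conclusion rests on three assumptions: that the sentence is applied as written; that the avoidance items are not reverse-keyed under a rule the article does not mention; and that more avoidance is not a favourable outcome in this population. The first two determine whether the error would reach the reported results. The wording needs correction in either case, because a reader cannot tell from the article which way a high avoidance score should be read.

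**What to change.** In the Proactive Coping Inventory paragraph, limit the direction sentence to the other six subscales and add one sentence for avoidance coping. Either of these would do:

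- state that a higher avoidance score means more avoidance and not better coping, and report this subscale separately on that basis; or
- state that its items are reversed (5 − x) before scoring, and in any event before any combination with other subscales.

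If the instrument's own key already reverses these items, saying so is enough.

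The cost is one sentence of text and, if reversal is chosen, one line of scoring code. Data collection and sample size are unaffected, and questionnaires already completed can be scored under the corrected rule. The direction should be fixed before the coping results are examined.
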